### Other measurement instruments

#### Collaboration between patient and care-provider

The level of collaboration between patient and care provider will be analyzed using the relationship scale from the working relationship questionnaire for case management [37], which consists of seven elements that are filled in by the care provider who is most familiar with the patient. The care provider responsible for the file is the one who is most familiar with the patient. In the CAU this is the patient's clinician. In the ACTE this is the clinician who gets to know the patient best after the intake procedure, and who is also the contact person for family and institutions.

#### Model fidelity of ACT

Research has shown that ACT has the best results when it is implemented in full according to the original ACT model [20,38-44]. As recommended in the literature, model fidelity will be determined on the basis of both conditions [20].

The fidelity of ACT and CAU will be measured twice (in 2010 and in 2011) by two independent researchers using the Dartmouth assertive community treatment scale (DACTS). The DACTS consists of 28 items covering three dimensions (team structure, organizational structure, and features of service delivery). All twenty-eight items are rated on a 5-point scale range from 1 (no implementation or only a low degree of implementation) to 5 (complete implementation) [45-47].

Table 2 shows an overview of all outcome measures and instruments.

**Table 2 T2:** Overview of outcome measurements

Variable	Instrument	Assessed by	Baseline	9 month	18 month
Socio-demographics	Patient records	Interviewer	X	X	X
Psychiatric history	Patient records	Psychiatrist or doctor	X		
Psychiatric	DSM IV Patient	Psychiatrist or	X	X	X
diagnosis	records	doctor			
Drop-out	Registration system	Researcher	X	X	X
Crisis contacts	Registration system	Researcher	X	X	X
Admission days	Registration system	Researcher	X	X	X
Psychosocial functioning	HoNOS 65+	Interviewer	X	X	X
Care need	CANE short version	Interviewer	X	X	X
Quality of life	QoL	Interviewer	X	X	X
Satisfaction with care	One question on 7- point Likert scale	Interviewer	X	X	X
Collaboration between patient and care-provider	Working Relationship Questionnaire for Case Management	Care provider	X	X	X
ACT model fidelity	DACTS	Trained ACT evaluators	X		X

### Power analysis

The sample size was determined by means of a power analysis. To detect a clinically significant impact (average effect size (Cohen's d) ≥ 0. 6) on the primary outcome variable (number of patients remain in care with an alpha of 0. 05 and a power of 0.85), we needed at least 50 patients per condition. In another ACT trial, Sytema et al [48] found 20% lose for randomization due to patients' failure to meet the inclusion criteria, and patients who refused to give informed consent for the interview [48]. We therefore wanted to include 80 patients in the ACTE team and 80 patients in the CAU condition. This will be enough to prove a clinically significant effect.

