The last limitation is the inclusion format. We started with the following inclusion criteria: (1) age 65 year or older; (2) having a severe mental illness, (3) no motivation for treatment, and (4) having four or more additional problems within the following domains: addiction, somatic problems, activities of daily living, housing, daytime activities, social relationships, finances, or police contacts. Untill June 2009 only 35 patients were included. Therefore we broadened our inclusion criteria by lowering the minimum age to 60 years. January 2010 only 50 patients were enrolled and we decided to limit the number of problems in several domains to 2 (was 4). Finally, in March 2010 we included only 56 patients, and then we let loose of criterion no 4. At the end of the trial by July 31 2010 we recruited 64 participants. Till August 1^st ^2010, fife patients died, 3 in the intervention group and 2 in the control group (no suicides). Because of the number of patients enrolled in this study (64 patients) the power of the study is a problem.

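### The assurance that the sample is large enough applies to an unmet target of 160; at the 64 recruited, power at d = 0.6 is about 66%, and the article never says so

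*Protocol article*

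**What the plan says.** The Power analysis section sizes the trial "on the primary outcome variable (number of patients remain in care"), using an "average effect size (Cohen's d) ≥ 0. 6" and an "alpha of 0. 05 and a power of 0.85". From these it derives that "we needed at least 50 patients per condition". It then cites another ACT trial with "20% lose for randomization due to" ineligibility and refusal of interview consent, and sets the target: "We therefore wanted to include 80 patients in the ACTE team and 80 patients in the CAU condition". The section closes with "This will be enough to prove a clinically significant effect".

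The Discussion, in its paragraph on the inclusion format, describes three successive relaxations of the entry criteria and a final count of 64 at the end of July 2010. It then says: "Because of the number of patients enrolled in this study (64 patients) the power of the study is a problem". The Procedure and timeline sections confirm that inclusion closed on 1 August 2010.

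No power or detectable effect for 64 patients appears anywhere in the article.

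**The concern.** A reader who wants the trial's power looks in the Power analysis section. There they find 85%, a target well above the minimum, and an unqualified assurance in the future tense. By the time the article was written the sample was fixed at 64 in total, fewer than the 100 (2 × 50) that the section itself calls the minimum. The admission in the Discussion does not tell the reader how large the loss is.

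The central question is whether ACTE keeps patients in care. At the effect that the plan itself calls clinically significant, the chance of missing it is about one in three, not the 15% behind the sample-size calculation. Without that figure, a non-significant comparison could be taken as stronger evidence of no benefit than 64 patients can give. The Background already cites European trials that found no difference between ACT and usual care, so this misreading is plausible.

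**Working it through.** **Inputs from the article**
- Effect size d = 0.6, alpha 0.05, power 0.85, 50 per arm, 20% loss, target 80 per arm (Power analysis)
- 64 recruited in total (Discussion)
- Equal allocation in blocks of four (Randomization)

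**Assumptions**
- Two-sided test. Sidedness is not stated, but this choice reproduces the stated 50; a one-sided test would need only 40–41 per arm.
- Split of 32/32. This is not stated, but 64/4 = 16 full blocks would give it.

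**1. Reproduce the stated size.** By the normal approximation, n per arm = 2(z₀.₉₇₅ + z₀.₈₅)²/d² = 2(1.960 + 1.036)²/0.36 = 49.9, so 50. The exact t-test gives 50.9, so 51. The stated figure is confirmed.

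**2. Power at a given n per arm.** By the normal approximation, power = Φ(d√(n/2) − 1.960).

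| Scenario | n per arm | d√(n/2) | Power (normal) | Power (t-test) |
|---|---|---|---|---|
| Stated minimum | 50 | 3.000 | 85.1% | 84.4% |
| Planned target | 80 | 3.795 | 96.7% | 96.5% |
| Target less 20% (80 × 0.8) | 64 | 3.394 | 92.4% | 92.0% |
| Recruited, 64 in total | 32 | 2.400 | 67.0% | 65.6% |

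The third row has 64 per arm; the last has 64 in both arms together.

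Type II error at d = 0.6 is therefore 1 − 0.656 = 34% with the recruited sample, against the 15% designed for.

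**3. Effect detectable with 85% power at 32 per arm.** d = (1.960 + 1.036)√(2/32) = 2.996 × 0.25 = 0.749 by the normal approximation, and 0.761 by the t-test.

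**4. Sensitivity to the assumptions**
- *Split.* With 30/34, √(n/2) is replaced by √(30 × 34/64) = 3.992. Power is Φ(0.6 × 3.992 − 1.960) = Φ(0.435) = 66.8%, hardly changed.
- *Sidedness.* One-sided power at 32 per arm would be about 77%, but that reading does not reproduce the stated 50.
- *Binary outcome.* Remaining in care is yes/no, whereas d is a scale for means. Reading 0.6 as Cohen's h needs 50–54 per arm for assumed control retention of 30–70%, and gives 64–66% power at 32 per arm. Converting d to an odds ratio (about 2.97) would give 39–57% over the same range, but needs 63–99 per arm, so it is not the calculation the article made.

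**The case against.** Much of the opposing case stands.

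- **The quoted sentence is not false in its place.** It follows directly on the 80 + 80 target, and for that target it is true. The 85% belongs to the 50-per-arm minimum. A reader might infer that the article claims 85% power for 64 patients, or that its sample-size arithmetic is wrong. Neither is supported.
- **The shortfall is disclosed.** The Discussion states it openly and names power as a problem. A plan followed by a reported shortfall is not a contradiction, and nothing is concealed. What remains is that the loss is not quantified and the sections are not linked.
- **Lower power figures are tempting but not established.** Taking a further 20% off the 64 (25.6 per arm) gives about 56–57%, and removing the five reported deaths (29.5 per arm) gives about 62–63%. The 20% covers ineligibility and interview refusal, whereas Table 2 takes drop-out from the registration system. The 64 are already described as enrolled, randomization precedes interview consent, and analysis is by intention to treat. The article does not say that deaths leave the drop-out analysis. These figures are at most low-end scenarios.
- **A retention example, such as 50% against 84%, would need a control rate that the article does not give.** It should not be presented as the trial's detectable difference.
- **How a non-significant result will be read may belong in an analysis plan that is not shown.** Its absence here is no defect. The reading rule below is a safeguard that follows from the reduced power.

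**Conclusion.** The point holds as a superseded assurance left unqualified and an acknowledged power loss left without a number. At d = 0.6 and two-sided alpha 0.05, 64 patients split 32/32 give about 66–67% power. To have 85% power, the true effect would have to be about 0.75–0.76 instead of 0.60. These are powers at the plan's own effect size, not powers computed from observed results. They rest on the two assumptions above, of which only sidedness matters much.

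This should be corrected, but it is not among the most serious kinds of fault: the calculation reproduces, the shortfall is admitted, and no design or analysis step has to change.

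**What to change.** In the Power analysis section:
- Keep the calculation of 50 per condition and the 80 + 80 target as the planning rationale.
- Qualify the closing sentence so that it applies to the 80 + 80 target, and say that this target was not met.
- Add that 64 patients were recruited, giving about 66% power at d = 0.6 (two-sided alpha 0.05, equal arms) and 85% power only for d of about 0.76. State the actual arm sizes and the sidedness.
- Cross-refer to the recruitment paragraph of the Discussion, and refer back from there.

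Before analysis, also state that the primary comparison will be read from the effect estimate with its 95% confidence interval, and that a non-significant result whose interval includes the target effect is inconclusive, not evidence of no effect. This requires the target on the scale of the outcome. Read as Cohen's h, 0.6 corresponds to a difference in retention of about 22 to 29 percentage points for assumed control rates of 30–70% (for example 92.4 − 70 = 22.4 and 59.4 − 30 = 29.4). The sponsor would have to supply the control rate.

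The cost is a few sentences and a less favourable stated power. No further patients are needed. The timeline puts data analysis after 1 March 2012, so the wording can be settled before then.

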### Randomization

The patients were referred to BavoEuropoort by general practitioners or other institutions (such as the police or municipal health service), who filled out a form describing the patient's characteristics and current problems. To determine whether the patients fulfilled the inclusion criteria, this form was reviewed using a checklist by the researcher (JS) and clinicians. If the patient did meet the criteria, he or she was allocated a number chronologically by the service administrator. Each number was given to the researcher, who then decided on the condition (intervention or care as usual). This was done on the basis of a previously arranged list of numbers randomized to each of the two conditions (with help from http://www.randomizer.org). To ensure similar numbers in both conditions the pre-arranged list of numbers are based on a block design (block size of four). Inclusion and randomization of patients was done before informed consent was obtained for participation in an interview with the interviewer.

### Statistical analysis

Analyses will be performed according to the *intention to treat *principle, which means that everyone who is randomized stays in the group in which they were randomized. Statistical package for the social sciences, version 15.0 will be used to analyze the data. The primary outcome measure is the differences between ACTE and CAU regarding the number of patients who were out-of-contact with mental health services. Secondary outcome measures are improvement of psychosocial functioning (total HoNOS 65+ score, total score from baseline to the final interview after 18 months), need-for-care over time (primary outcome measures), the number of crisis contacts and (in)voluntary admissions, and the number of admission days (these last 3 measures will be retrieved from administration files) The interviewer collects the other secondary outcome measures (subjective quality of life and client satisfaction.) Categorical variables shall be analyzed using chi-square tests. Mixed models with repeated measurement were applied for the continuous outcomes. This model will be used because of the ability to include participants with missing data. Missing data at the second and third interview will be imputed with the last carried out interview.

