**Methods:**

We will use a randomized controlled trial design to compare the effects of assertive community treatment for the elderly with those of care as usual. Primary outcome measures will be the number of dropouts, the number of patients engaged in care and patient's psychiatric symptoms, somatic symptoms, and social functioning. Secondary outcome measures are the number of unmet needs, the subjective quality of life and patients' satisfaction. Other secondary outcomes include the number of crisis contacts, rates of voluntary and involuntary admission, and length of stay. Inclusion criteria are aged 65 plus, the presence of a mental disorder, a lack of motivation for treatment and at least four suspected problems with functioning (addiction, somatic problems, daily living activities, housing etc.). If patients meet the inclusion criteria, they will be randomly allocated to either assertive community treatment for the elderly or care as usual. Trained assessors will use mainly observational instruments at the following time points: at baseline, after 9 and 18 months.

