### Hypotheses

Our first hypothesis is that ACTE will decrease the number of patients who drop out of care (number of patients who have no registered contact with the services over a period of 3 months and/or the number of patients discharged out of care). The other primary hypotheses include that ACTE will increase the number of patients engaged in care (patients who receive care within 3 months after admission to the team) and will improve patients' psychiatric, somatic and social symptoms. Secondary hypotheses include that ACTE reduce the number of unmet needs more than CAU does. We also expect an increase in patients' subjective quality of life and in patients' satisfaction with mental-health care. Finally we hypothesize that to a greater extent than CAU, ACTE will reduce the number of crisis contacts, reduce voluntary and involuntary admission rates and reduce length of stay in a psychiatric hospital.

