### Outcomes and measurement instruments

Our primary outcome measures will be the number of dropouts (drop-out being defined as no registered contact with the services over a period of 3 months and/or the number of patients discharged out of care). The number of patients who are engaged in care (patients who receive care within 3 months after admission) and patient's psychiatric symptoms, somatic symptoms, and social functioning.

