#### Our secondary outcomes measures will be

1. The number of unmet needs,

2. Subjective quality of life,

3. Patients' satisfaction with mental-health care,

4. The number of crisis contacts and (in)voluntary admissions, and the number of admission days. The admission days and crisis contacts were calculated during two periods of observation. The first period was the year before inclusion in the study. The second was the variable observation period ranging till 2 years after inclusion. In both periods, the admission data were standardized as mean number of days per month and crisis contacts as mean number.

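### The article gives conflicting outcome hierarchies, so a benefit on HoNOS 65+, engagement or need-for-care alone is primary under one reading of the text and secondary under another

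*Protocol article*

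**What the plan says.** All places are in the protocol article.

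- **Abstract, Methods:** "Primary outcome measures will be the number of dropouts, the number of patients engaged in care and patient's psychiatric symptoms, somatic symptoms, and social functioning". Unmet needs are secondary.
- **Hypotheses:** drop-out comes first, counted as three months without registered contact and/or discharge. Then: "The other primary hypotheses include that ACTE will increase the number of patients engaged in care", with psychiatric, somatic and social symptoms in the same group. Unmet needs fall under the secondary hypotheses.
- **Outcomes and measurement instruments:** drop-out (same definition), engagement, and "patient's psychiatric symptoms, somatic symptoms, and social functioning" are primary. The secondary list opens with "The number of unmet needs".
- **Power analysis:** one primary outcome variable, patients remaining in care, with alpha 0.05, power 0.85 and Cohen's d of 0.6, giving 50 per condition.
- **Statistical analysis:** "The primary outcome measure is the differences between ACTE and CAU regarding the number of patients who were out-of-contact with mental health services". Psychosocial functioning, as the HoNOS 65+ total, is secondary. Need-for-care stands in that same list of secondaries but carries a primary tag: "need-for-care over time (primary outcome measures". Engagement is not named.
- **Discussion:** the central question joins remaining in care with psychosocial symptoms and unmet needs.

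**The concern.** Psychosocial functioning is primary in three sections and secondary in a fourth. Need-for-care carries both labels in one sentence. Engagement is primary in three sections and is not a primary in the analysis section. These statements cannot all hold, and the article does not say which governs.

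The practical case is a trial that misses on retention and shows a benefit on HoNOS 65+. Under the Outcomes section that is a primary success. Under the Statistical analysis section it is a secondary finding after a failed primary.

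The case is realistic. The Discussion reports 64 recruited against 160 planned and concedes a power problem. It also says the research assessor, who rates HoNOS 65+, is not blinded. An ambiguous hierarchy therefore leaves an unblinded rating available as a second route to a positive claim. It also leaves unclear how many tests share the stated 5% error rate.

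**Working it through.** **1. The plan's own sample size.** Inputs from the Power analysis: d = 0.6, alpha 0.05, power 0.85, one outcome. Sidedness is not stated.

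n per arm = 2(z₁₋α/₂ + z₁₋β)² / d²

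- Two-sided: 2(1.960 + 1.036)² / 0.36 = 49.9, so **50**, the stated figure. An exact t-test calculation gives 50.9.
- One-sided: 2(1.645 + 1.036)² / 0.36 = 39.9, so 40, which does not match.

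The plan's 50 is thus a calculation for one outcome at two-sided 0.05.

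**2. How many primaries the multiple-primary sections imply.**

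- Five, if psychiatric, somatic and social functioning are separate outcomes, as the Abstract, Hypotheses and Outcomes sections word them.
- Three (drop-out, engagement, HoNOS 65+ total), if the three domains form one variable. The Assessment instruments section and Table 2 treat them so, and the Statistical analysis section names only the total score.
- Counting need-for-care as tagged makes these six or four.

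**3. Chance of at least one false positive, assuming each is tested unadjusted at 0.05.** For k independent tests it is 1 − 0.95^k.

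- k = 3: 1 − 0.857 = **14.3%**
- k = 4: 18.5%
- k = 5: 1 − 0.774 = **22.6%**
- k = 6: 26.5%

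For five correlated two-sided tests (400,000 simulated sets of equicorrelated normal statistics, threshold 1.96):

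- correlation 0.3: 21.0%
- correlation 0.5: 18.3%
- correlation 0.7: 14.9%
- correlation 0.9: 10.1%

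The article gives no correlation, so these values are assumptions and the whole range should be read.

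**4. What several primaries would need under a Bonferroni split** (same d and power).

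- Three tests at 0.0167: 66 per arm
- Five tests at 0.01: 73 per arm

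With about 32 per arm (64 recruited, equal split assumed), power at d = 0.6 is 67% for one outcome at 0.05. Per test it is 50% with three primaries and 43% with five.

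**5. The retention endpoint across sections.** The Hypotheses and Outcomes sections count three months without contact and/or discharge. The Statistical analysis section speaks only of being out of contact, with no duration and no mention of discharge. The Power analysis speaks of remaining in care. The construct is broadly the same, but it has three wordings and only one of them is a definition.

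**The case against.** The strongest reply is that retention is primary wherever a primary is named. It is also the first hypothesis and the basis of the sample size. A reader might infer that the trial's whole verdict depends on which section is followed, and that goes too far: a retention result keeps its status throughout. This part of the reply stands.

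A reader might also infer that five outcomes will each be tested at 0.05. The article does not say so. Its only alpha is attached to the sample-size variable, and a multiplicity rule could sit in an analysis plan that is not shown. The three domains are also measured with one instrument and analysed as one total, so three primaries is at least as fair a count as five. Both points stand, which is why the error rates above are conditional and 22.6% is not the headline figure.

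Engagement's absence from the analysis paragraph is weak evidence on its own. It is listed for collection, and the chi-square rule for categorical variables would cover it.

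None of this removes the conflict. The article states its hierarchy several times and states it differently, which is not condensation. A separate analysis plan could choose one version only by contradicting another.

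**Conclusion.** The point holds as a contradiction in outcome labels, and that part needs no arithmetic. Psychosocial functioning, engagement and need-for-care have no settled status, so a benefit on any of them alone could be reported as primary or secondary depending on the sentence relied on.

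The size is conditional. On the assumption of unadjusted tests at 0.05, the chance of at least one false positive is 14.3% for three independent primaries and 22.6% for five. For five it is about 21% to 10% under assumed common correlations of 0.3 to 0.9. The documents do not establish that such testing is planned. With one primary the error rate stays at 5% and the stated 50 per arm is consistent, so the sample size supports the single-primary reading.

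**What to change.** - Name drop-out from care as the single primary outcome in the Abstract, Hypotheses, Outcomes, Power analysis and Statistical analysis sections.
- Give it one definition, and reconcile the version with three months without contact and/or discharge with the out-of-contact and remaining-in-care wordings.
- Label engagement, HoNOS 65+ and need-for-care secondary throughout, and delete the primary tag after need-for-care.
- Record this as a dated, justified change before outcome analysis. The timeline puts data analysis from 1 March 2012. Because recruitment had closed and the assessor is not blinded, the date and reason matter as much as the wording.

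Keeping several primaries with a stated multiplicity rule would also be valid, but it fits the sample size poorly: 66 to 73 per arm under Bonferroni, against about 32 recruited. How HoNOS 65+ subscales are ranked among the secondaries is a matter of preference.

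The cost is consistent wording and one documented amendment. The small downside is that a benefit on HoNOS 65+ or engagement alone can no longer be called a primary result.

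### The primary drop-out comparison is fixed as an unadjusted chi-square in 64 patients although age, and possibly problem-domain count, were available before allocation; some precision may be left unused

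*Protocol article*

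**What the plan says.** The Statistical analysis section of the protocol article takes as primary outcome the difference between arms "regarding the number of patients who were out-of-contact with mental health services". For outcomes of this type it fixes the method: "Categorical variables shall be analyzed using chi-square tests". No covariate or stratum is named, and mixed models are kept for continuous outcomes. The Outcomes section lists a second binary primary outcome, which falls under the same rule: "The number of patients who are engaged in care (patients who receive care within 3 months after admission".

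The Power analysis section asks for at least 50 patients per condition, based on "average effect size (Cohen's d) ≥ 0. 6" "with an alpha of 0. 05 and a power of 0.85". The Discussion reports 64 recruited and concedes: "Because of the number of patients enrolled in this study (64 patients) the power of the study is a problem". It offers no analytic remedy.

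On what was known before allocation, the Randomization section says that patients came from referrers "who filled out a form describing the patient's characteristics and current problems". That form was checked against the inclusion criteria before a number was issued. Allocation used blocks of four, and no stratification is described.

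The Discussion also reports three changes to eligibility. After 35 patients, "Therefore we broadened our inclusion criteria by lowering the minimum age to 60 years". The required number of problem domains fell from four to two after 50 patients, and the domain criterion was dropped after 56.

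**The concern.** Recruitment is closed well short of target, so the analysis is one of the few places where precision can still be gained. An unadjusted chi-square ignores everything known about a patient before randomisation. If age or number of problem domains predicts drop-out, a pre-specified adjusted analysis is somewhat more powerful and removes chance imbalance on those variables, which unstratified blocks of four do not control.

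In this Zelen design it matters which baseline values are used. Referral and checklist values precede allocation and do not depend on consent to the interview. The first HoNOS 65+ rating is made at a visit arranged after randomisation, so it is not a clean baseline covariate.

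**Working it through.** **Inputs from the protocol.** d = 0.6, alpha 0.05, power 0.85, 50 per condition (Power analysis); 64 recruited, with eligibility changes after 35, 50 and 56 patients (Discussion); 1:1 blocks of four (Randomization). **Assumed, because not given:** 32 per arm, two-sided alpha, the drop-out rates, and the prognostic strength of the covariates.

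**1. The plan's own figure.** n per arm = 2 × ((1.960 + 1.036)/0.6)² = 49.9, so 50. The stated figure reproduces with two-sided alpha; one-sided alpha would give 40.

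**2. Unadjusted power with 32 per arm.** Φ(0.6 × √(32/2) − 1.96) = Φ(2.40 − 1.96) = Φ(0.44) = 0.67. Reading 0.6 as a difference between proportions (Cohen's h) gives 0.64 to 0.66 for control rates of 30% to 60%.

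**3. What adjustment could add, by approximation.** If covariates explain a share R² of outcome variance, power = Φ(2.40/√(1 − R²) − 1.96). This gives 0.68 at R² = 0.02, 0.69 at 0.05, 0.72 at 0.10 and 0.77 at 0.20. Restoring 0.85 needs R² = 1 − 32/49.88 = 0.36.

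**4. Simulation with a fixed conditional effect.** 32 per arm, control rate near 50%, treatment odds ratio 1/3.5, one prognostic and one useless covariate. The logistic likelihood-ratio test was run on 2,000 trials per setting and a linear risk-difference test on 4,000, each against its own chi-square.

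| Covariate odds ratio per SD | Chi-square | Logistic | Gain (points) | Chi-square | Linear | Gain (points) |
|---|---|---|---|---|---|---|
| 1 | 0.669 | 0.664 | −0.5 | 0.637 | 0.620 | −1.7 |
| 1.5 | 0.628 | 0.644 | +1.6 | 0.637 | 0.634 | −0.3 |
| 2 | 0.596 | 0.638 | +4.2 | 0.581 | 0.597 | +1.6 |
| 3 | 0.511 | 0.589 | +7.8 | 0.511 | 0.567 | +5.6 |

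A repeat gave logistic gains of about 2, 3.5 and 8 points and linear gains of about 0.5, 1 and 4.5 at odds ratios 1.5, 2 and 3. The Monte Carlo error of one power figure at 2,000 trials is √(0.63 × 0.37/2000), about 1.1 points, so differences near one point should not be read closely.

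**5. Simulation with fixed marginal rates.** With 50% versus 22% drop-out (3,000 trials per setting), chi-square power stays at 0.63 to 0.66. The adjusted logistic test has 0.65 at R² = 0, 0.67 at 0.06, 0.70 at 0.17, 0.79 at 0.29 and 0.84 at 0.39. The direction agrees with step 4.

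**6. Type I error.** Near a 50% event rate the two tests are alike: 5.4–6.7% for chi-square and 5.2–6.3% adjusted in the step 4 logistic run. At 20%, the logistic test rejects a true null 5.8–6.4% of the time against 4.9–5.4%. At 10%, it is about 7–8.5% against 5–6%. With a treatment odds ratio of 1/3.5, about 37–39% of trials at 10% give near-separated fits (9–11% at 20%).

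**7. Spread of the covariates.** From the recruitment counts, at most 64 − 35 = 29 patients could be aged 60 to 64. At most 64 − 50 = 14 could have fewer than four domains, and at most 64 − 56 = 8 entered with no domain requirement.

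**The case against.** The chi-square is a valid test for this comparison, so nothing in the plan is wrong in the strict sense. The sentence is generic, the document is a condensed article, and an SAP might add adjusted analyses. This stands as to validity. But the method is stated rather than left open, and the same article calls power a problem, so the choice can fairly be questioned.

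A reader might infer several stronger points that the document does not support:

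- *That age and domain count vary widely after the eligibility changes.* No distribution is reported, and at least 50 of 64 patients entered under the four-domain rule.
- *That all problem domains are on record for everyone.* The form described current problems and the checklist decided eligibility. A threshold check needs no full count, and once the domain criterion was dropped no count was needed at all. Only age is secure, because an age limit applied throughout.
- *That power is certainly being lost.* Nothing in the document links age or domain count to drop-out. With no association, adjustment costs a little.
- *That adjustment deals with the changing entry criteria.* Terms for age and count do not model recruitment period or differing treatment effects.
- *That a logistic model should become the main test for both binary outcomes.* The engagement rate is not given, and if either category is rare the logistic likelihood-ratio test over-rejects.

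A further caution is that the researcher who reviewed the checklist also held the allocation list. The values precede allocation, but the document does not show that they were recorded without knowledge of it. This matters more for a judged domain count than for age.

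**Conclusion.** The point holds in a limited form. The plan fixes an unadjusted test for its primary binary outcome at a sample size that gives about 0.67 power for the design effect instead of 0.85, while at least one pre-randomisation covariate is available without new data. The plausible benefit of logistic adjustment is about 2 to 4 points of power at covariate odds ratios of 1.5 to 2 per SD and about 8 points at 3, against a possible loss of about 0.5 to 2 points. A linear risk-difference analysis gains less.

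These figures rest on 32 per arm, a control drop-out rate near 50% and assumed prognostic strength. The gain is modest and conditional; 0.85 would be regained only if the covariates explained about 36% of outcome variance. The case for adjustment covers drop-out and does not carry over automatically to engagement.

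**What to change.** Before outcomes are analysed:

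- **Drop-out:** pre-specify an analysis adjusted for age. Add the checklist domain count only if it proves to have been recorded before allocation for essentially all patients. Report a standardised risk difference with 95% CI alongside the chi-square.
- **Engagement, or either outcome if its event rate is about 20% or less:** keep the chi-square, or use an adjusted linear risk-difference analysis or a penalised or permutation test, rather than the logistic likelihood-ratio test. The rule can be written on the pooled rate of the rarer category, without reference to arm.
- **Baseline HoNOS 65+:** do not use it as a covariate, because it is rated after allocation.

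The cost is a few lines of analysis text, entry of one or two items from existing referral forms, a check of how completely the domains were recorded, and the small power loss already given if neither item is prognostic. The Discussion should still present the study as underpowered.
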